### Blinding

With exception of the team in the operating theater, all involved medical and non-medical practitioners are blinded as well as the patient. The procedure will be named as *laparoscopic Roux-en-Y gastric bypass* in all medical records without mentioning the limb lengths. Unblinding is permitted at the end of the study and in case of surgical or medical complications, emergency consultation, or other ethical considerations. The operating surgeon will not be involved in any decisions that influence the primary endpoint or in judgement of the primary endpoint. Furthermore, the efficacy of blinding measures will be regularly assessed according to by Probst et al. [24].

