### Study visits

Physicians blinded to the intervention will perform study documentation and patient assessment. Since the trial is designed as an observer and patient blinded RCT, information about the surgical procedure will not be disclosed during the follow-up examinations to any assessors. There will be 11 study visits in total. The study design flow diagram is presented in Table 1. Potential study participants will be identified by the preoperative outpatient clinic consultations. The first visit will be preoperative after informed consent is obtained. Then patients will receive their study intervention according to the preoperative randomization. Postoperatively, study visits will be performed at discharge, 3, 6, 9, 12, and 18 months and 2, 3, 4, and 5 years. Each study visit includes data collection of weight, blood tests (e.g., hemoglobin, creatinine, urea, uric acid, calcium, C-reactive protein, albumin, liver function tests, fasting glucose, HbA1c, vitamins A, B1, B6, B12, and D, parathormone, ferritin, folate, zinc, cholesterol, lipoproteins, and triglycerides), and complications. In addition, questionnaires will be also assessed to study the quality of life (Bariatric Analysis and Reporting Outcome System [BAROS] [18] and the Gastrointestinal Quality of Life Index [GIQLI] [19]), the Arts questionnaire [20] to determine postoperative determine dumping syndrome and questionnaire for quantification of frequency and severity of potential diarrhea.

**Table 1 Tab1:** Schedule of study assessments

Study periods	Screening	Intervention	Follow-up								
Visit	1	2	3	4	5	6	7	8	9	10	11
Time (day, month, year)	− 3 months	0–5 days	3 months	6 months	9 months	1 year	1.5 years	2 years	3 years	4 years	5 years
Patient information and informed consent	x										
Demographics	x										
Medical history	x										
Inclusion/exclusion criteria	x	x									
Physical examination	x	x	x	x	x	x	x	x	x	x	x
Vital signs	x	x	x	x	x	x	x	x	x	x	x
Laboratory tests	x	x	x	x	x	x	x	x	x	x	x
Randomization		x									
Operation		x									
Complications		x	x	x	x	x	x	x	x	x	x
Primary variables	x	x	x	x	x	x	x	x	x	x	x
Secondary variables	x	x	x	x	x	x	x	x	x	x	x
Questionnaires	x			x		x		x	x	x	x
Adverse events		x	x	x	x	x	x	x	x	x	x

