### Study endpoints

#### Primary endpoint

The primary endpoints are %TWL and the number of nutritional deficiencies 1, 3, and 5 years postoperatively. For the %TWL the presurgical weight (at hospital entry time of the patient) and postsurgical weight at the corresponding visit will be measured.

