#### Secondary endpoints

%EBMILRemission of comorbiditiesComplication rateQuality of life

All comorbidities will be assessed at 3, 6, 9, 12, and 18 months and 2, 3, 4, and 5 years by a physician based on symptoms, laboratory findings, and use of medication. The postoperative course of comorbidities will be defined as follows: remission: no symptoms/without any medication (dyslipidemia true remission = no medication and normal lipid values); remission of T2DM will be defined according to the ADA criteria: complete remission: HbA1c < 6.0%, fasting glucose < 100 mg/dl and at least one year no active pharmacologic therapy; partial remission HbA1c < 6.5% [21]; improvement: less symptoms and/or less medical treatment/medication; unchanged: same symptoms and equivalent therapy; worsened: more symptoms or increase of therapy; de novo comorbidity: comorbidity not present at baseline, but newly developed within 5 years postoperatively. All surgical and non-surgical complications will be assessed according to the Clavien-Dindo classification (CDC) [22] and the Comprehensive Complication Index (CCI) [23]. The Arts score will help to identify potential dumping syndrome. BAROS and GIQLI scores will be used to measure postoperative quality of life.

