### Statistical analyses

#### Sample size

Our study was designed to evaluate whether long BPL in RYGB has advantages compared to short BPL in terms of % weight loss (superiority) without compromising the safety in terms of nutritional deficiency rate (non-inferiority) at 5 years follow-up. For our primary outcome efficacy and safety, assuming a %TWL of 27 ± 10% at 5 years follow-up for short BPL with a minimal improvement of 5% TWL for long BPL to be relevant and an expected cumulative nutritional deficiency rate of 50% at 5 years follow-up with a non-inferiority margin defined at 10%, 400 patients per group will be needed to reach a power of 80% with an alpha level at 5%. For further details on calculations, see the “Analysis of endpoints” section below.

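### The unblinding clause has no clinical-need condition and no limit on who is told, so an endpoint event can itself open the blind

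*Protocol article*

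**What the plan says.** The Blinding section sets a wide blind: "With exception of the team in the operating theater, all involved medical and non-medical practitioners are blinded as well as the patient". It then lists when the blind may be opened: "Unblinding is permitted at the end of the study and in case of surgical or medical complications, emergency consultation, or other ethical considerations". The same section adds two safeguards: "The operating surgeon will not be involved in any decisions that influence the primary endpoint or in judgement of the primary endpoint", and "the efficacy of blinding measures will be regularly assessed". It also has the operation recorded under a neutral name without limb lengths.

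The Study visits section states, without exception, that "information about the surgical procedure will not be disclosed during the follow-up examinations to any assessors".

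On outcomes, the Primary endpoint section says "The primary endpoints are %TWL and the number of nutritional deficiencies 1, 3, and 5 years postoperatively". The Sample size section plans on "an expected cumulative nutritional deficiency rate of 50% at 5 years follow-up", with a 10% non-inferiority margin. Complication rate is a secondary endpoint, and under that heading "All surgical and non-surgical complications will be assessed according to the Clavien-Dindo classification" and by the Comprehensive Complication Index. Comorbidity course is rated by a physician from symptoms, laboratory findings and medication use. Quality of life comes from BAROS and GIQLI.

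**The concern.** The clause names kinds of event and does not ask whether knowing the limb lengths would help in handling them. A complication of any grade qualifies, so does any emergency visit, and the last item is open-ended. The clause is also silent on whether disclosure goes to the treating clinician alone or also to the patient and the follow-up physician.

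The complication trigger describes almost the same set of events as the secondary complication endpoint. A site that follows the clause as written may therefore unblind a patient because an outcome occurred. If outcomes differ between the arms, which is what the trial is set up to find out, eligibility for unblinding will differ too. Patients and physicians who know the arm may then report symptoms, adjust medication, rate comorbidities or look for deficiencies differently, and this loss of blinding would be uneven between the arms over a 5-year follow-up.

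**Working it through.** **Step 1. The plan's own figure.** Inputs from the Sample size section: deficiency rate 50%, margin 10% (taken as percentage points), power 80%, alpha 5% (taken as one-sided 0.025, since the sidedness is not stated).

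n per arm = (1.960 + 0.842)² × 2 × 0.5 × 0.5 / 0.10² ≈ 393

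The stated 400 per group is reproduced to within 2%, and power at 400 per arm is 80.7%. The efficacy part (difference 5, SD 10) needs only 63 per arm, so the deficiency comparison drives the sample size. None of this depends on the unblinding rule.

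**Step 2. Trigger against endpoints.**

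| Outcome | Where defined | Covered by the unblinding trigger? |
|---|---|---|
| Complications, any grade | Secondary endpoints | Yes, on the plain wording |
| Nutritional deficiency | Primary endpoint; Sample size | Not stated; the clause can be read to include it |

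For complications no inference is needed. For deficiencies the text is open. Study visits lists blood tests and complications as separate items, and the endpoint sections keep them apart. On the other hand, the Sample size section treats deficiency as the safety measure, the Analysis of primary endpoint section calls these safety events, and the Background and Discussion describe malnutrition as the risk of a longer biliopancreatic limb. Nothing in the Blinding section excludes deficiencies.

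**Step 3. How many patients the deficiency route could reach.**

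Eligible by 5 years, at most: 800 × 0.50 = 400.

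Let f be the share of these patients whose deficiency is treated as a complication and who are unblinded. The documents give no value for f, so every value is an assumption.

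| f | Patients unblinded = 400 × f |
|---|---|
| 0 | 0 |
| 0.10 | 40 |
| 0.25 | 100 |
| 0.50 | 200 |
| 1 | 400 |

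Other complications and emergency visits would add to this. The article gives no expected rate for them.

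**Step 4. Difference by arm.** With 50% in both arms, 400 × 0.50 = 200 patients per arm become eligible. If the long-limb arm lay at the margin, at 60%, it would have 400 × 0.60 = 240, against 200 in the short-limb arm. This only illustrates that eligibility follows the outcome. It does not predict a difference.

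**Step 5. Which outcomes are exposed.**

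- Largely unaffected: measured weight, blood values from scheduled tests, and a first deficiency, which is already in the cumulative rate before it can lead to unblinding.
- Exposed: comorbidity ratings that rest on symptoms and medication, BAROS and GIQLI, later care, and later deficiency counts at 3 and 5 years if the number of deficiencies is analysed as a count.
- A smaller route to the cumulative rate: a patient unblinded for an unrelated complication before any deficiency may be cared for differently afterwards.

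**The case against.** The strongest reply is that the clause permits unblinding and does not require it, that the article surrounds it with safeguards, and that the full protocol may hold the procedure. Much of this stands. Who authorises unblinding, how it is logged, who assesses the patient afterwards and how counts are reported are details that an article may leave out, and their absence is not criticised here. The safeguards are real, but they do not limit the trigger. One covers only the operating surgeon. Regular checks of blinding can detect a loss but do not prevent it. The neutral name in the records does not govern disclosure once unblinding is permitted.

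A reader might infer four stronger points that the article does not support:

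- **That a nutritional deficiency is a medical complication under the clause.** No section says so, and the two are listed separately. The most that can be said is that the wording leaves the reading open.
- **That the Blinding and Study visits sections contradict each other.** Both hold if only the treating clinician is told. The text does not say that this is what happens.
- **That the non-inferiority comparison is biased because the endpoint opens the blind.** A first deficiency found on a scheduled blood test has been counted before any disclosure it could prompt.
- **That a particular number of patients will be followed open-label, or that the trial cannot be called blinded.** The share unblinded is unknown, and the Study visits section bars disclosure to assessors.

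**Conclusion.** The concern holds as a fault in a stated rule. As written, the clause allows unblinding to be triggered by an outcome. This is certain for complications, and possible for nutritional deficiencies if sites read the clause that way. Through deficiencies, at most about 400 of 800 patients become eligible by 5 years. The number unblinded by that route is anywhere from 0 to 400. The upper limit rests on the plan's 50% rate, and on every deficiency being classed as a complication and then leading to disclosure.

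The consequence falls mainly on secondary outcomes that depend on judgement or self-report, and on later care and later deficiency counts. A differential effect also requires that complications or deficiencies differ by arm. The weight-loss endpoint and the cumulative deficiency rate are largely protected by how they are measured. The sample size is unaffected. The clause should be tightened because the change is cheap and the loss of blinding, once it occurs, cannot be undone.

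**What to change.** Reword the unblinding sentence in the Blinding section so that, before the end of the study:

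- allocation is disclosed only when the treating clinician needs the limb lengths to manage that patient;
- an endpoint event, whether a complication or a nutritional deficiency, does not qualify on its own;
- disclosure goes only to that clinician, and the patient and follow-up assessors stay blinded where possible.

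Add to the Study visits section that the bar on disclosure to assessors continues to apply after such an unblinding, so that the two sections read together.

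The cost is a one-paragraph amendment and slightly more work at the site when an event occurs. Access to the limb lengths when they are clinically needed is kept. The change concerns only who learns the allocation and when, and it prescribes no treatment.

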### Study management and administration

Data management and monitoring is supported by the CTU of the University of Basel. Source data of every study participant are entered into the study data management system secuTrial® (interActive Systems GmbH, Berlin, Germany).

### Quality control measures

Continuous central and on-site monitoring of the study is performed by the CTU for quality control and assurance purposes to evaluate the progress of the study and to verify the accuracy and completeness of eCRFs. All assessors will be trained in data entry to ensure data quality. Data entered into the eCRF will be validated for completeness and discrepancies automatically. Furthermore, the data will be reviewed by the responsible investigator as well as by an independent monitor. Furthermore, the CTU will ensure that all protocol requirements are met, and all applicable local authority regulations and investigator’s obligations are being fulfilled and to resolve any inconsistency in the study records. Monitoring will consist of one initiation visit, one monitoring visit per year, and a close-out visit per center as a minimum.

### Statistical analyses

#### Sample size

Our study was designed to evaluate whether long BPL in RYGB has advantages compared to short BPL in terms of % weight loss (superiority) without compromising the safety in terms of nutritional deficiency rate (non-inferiority) at 5 years follow-up. For our primary outcome efficacy and safety, assuming a %TWL of 27 ± 10% at 5 years follow-up for short BPL with a minimal improvement of 5% TWL for long BPL to be relevant and an expected cumulative nutritional deficiency rate of 50% at 5 years follow-up with a non-inferiority margin defined at 10%, 400 patients per group will be needed to reach a power of 80% with an alpha level at 5%. For further details on calculations, see the “Analysis of endpoints” section below.

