**Methods/design:**

The trial is designed as a multicenter, randomized, patient- and observer-blinded trial. The relevant ethics committee has approved the trial protocol. To demonstrate that long BPL RYGB is superior compared to short BPL RYGB in terms of weight loss and resolution of T2DM, the study is conducted as a superiority trial. Postoperative percent total weight loss and nutritional deficiency rate are the primary endpoints, whereas morbidity, mortality, remission of obesity-related comorbidities and quality of life are secondary endpoints. Eight hundred patients, between 18 and 65 years and with a body mass index (BMI) from 35 to 60 kg/m^2^ who meet the regulatory rules for bariatric surgery in Switzerland, will be randomized. The endpoints and baseline measurements will be assessed pre-, intra-, and postoperatively.

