### Interventions

All patients will receive standard preoperative assessment including endocrine, pulmonary function and cardiovascular assessment, psychiatric assessment, gastroscopy with Helicobacter pylori testing, and abdominal ultrasound to check for liver size and gallstones. Patients in arm A will receive a RYGB with a 180-cm-long BPL and an AL of 80 cm; the group B will receive a RYGB with an 80-cm BPL and a 180-cm AL. The individual technique in terms of trocar position, materials used (i.e., staplers, trocar, suture) will be left to the choice of each individual surgeon. Total small bowel length will be measured during surgery; patients with a total small bowel length of less than 440 cm will be excluded from the study. Patient- and observer-blinded pre- and postoperative follow-up will be performed. There are no strategies for patients to improve adherence to intervention protocol since this is a surgical trial. All participating centers and surgeons are experienced bariatric surgeons with a minimal total caseload of more than 200 bariatric procedures and more than 50 surgeries per year. In order to make surgeons adhere to intervention protocol, all critical surgical steps (e.g., pouch size, total bowel length measurement, technique of Roux-limb and gastroenterostomy construction, closure of mesenteric defects, and operation time) will be documented in our database. The non-adherent cases will be excluded from per-protocol analysis. There will be no criteria for modifying the operative procedures.

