### Ethical considerations

Participation in this trial is strictly voluntary and patients are allowed to exit the trial at any point without explanation. All eligible patients are provided an information brochure describing the study with sufficient information for them to make an informed decision about their participation in this study.

The study protocol, patients’ information sheets and informed consents were approved by the local ethic committee (Ethikkommission Nordwest- und Zentralschweiz, EKNZ 2019-02392). In addition, insurance coverage for general liability has been obtained.

Patients who decline to participate in this study are treated according to clinical standards. These patients will not be included and no study-specific follow-up will be performed.

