## Trial status

Protocol version number 1.1, 12 February 2020. The trial has received ethics approval by January 2020. The first patient will be randomized in June 2020. We expect to enroll the calculated sample size in a 2- to 3-year time period. Estimated end of the study is December 2027.

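### The 400 per group is, on the most direct reading, the evaluable number for non-inferiority with about 2% to spare, while the plan's own rules and the slow end of its timetable leave fewer patients with a 5-year outcome

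*Protocol article*

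**What the plan says.** The Sample size section covers two co-primary questions at 5 years: superiority on %TWL (27 ± 10% in the short-limb arm, 5 points better to be relevant) and non-inferiority on a cumulative nutritional deficiency rate (50% expected, margin 10%). It concludes that "400 patients per group will be needed to reach a power of 80% with an alpha level at 5"%. It does not say whether alpha is one- or two-sided and mentions no allowance for loss. It refers to Analysis of endpoints for details of the calculation, but that section contains none. The abstract (Methods/design) gives the number to be randomised: "Eight hundred patients, between 18 and 65 years" of age and within the BMI limits, so 400 per group is the randomised number.

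Other sections describe how patients may fail to contribute a 5-year outcome:

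- Ethical considerations: "patients are allowed to exit the trial at any point without explanation".
- Interventions: "patients with a total small bowel length of less than 440 cm will be excluded from the study". This is measured during surgery, as is the common-limb limit under Exclusion criteria, whereas Study visits describes randomisation as preoperative.
- Analysis of endpoints: the per-protocol population drops protocol violators and anyone with missed measurements.
- Trial status, on enrolment: "We expect to enroll the calculated sample size in a 2- to 3-year time period", with the first randomisation planned for June 2020. The same section says on completion: "Estimated end of the study is December 2027".

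**The concern.** If 400 is the number that must be evaluable, and it is also the number randomised, the stated 80% power needs almost complete 5-year outcome data. The plan expects withdrawals, removes some patients after randomisation, and gives an enrolment range whose slow end does not fit its end date. The half of the primary objective that sets the sample size, the claim that a longer limb does not raise the deficiency rate beyond the margin, would then have less power than stated. If the study did close on the estimated date after slow accrual, 5-year data on the last patients would not be collected and could not be recovered later.

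**Working it through.** **Inputs.** From Sample size: deficiency rate 0.50, taken as equal in both arms; margin 0.10, taken as absolute; power 80%; alpha 5%; %TWL difference 5, SD 10. From Randomization: allocation 1:1. From Trial status: June 2020, 2 to 3 years, December 2027. Loss rates are not given, so those below are assumptions.

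**1. Reproducing the 400.** Non-inferiority of two proportions, per group:

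n = (z₁₋α + z₀.₈₀)² × 2p(1 − p) / margin²

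- One-sided 2.5%: (1.960 + 0.842)² × 0.5 / 0.01 = 392.4, so 393.
- One-sided 5%: (1.645 + 0.842)² × 0.5 / 0.01 = 309.1, so 310.

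The first lies within 2% of 400. Other versions of the formula at one-sided 2.5% run from about 390 (null-variance form) to 402 or 412 (continuity corrections), so the exact spare number depends on the method. The second comes near 400 only if an allowance of about 20 to 22.5% is added (310/0.80 = 388; 310/0.775 = 400).

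**2. Superiority on %TWL.** n = 2 × 2.802² × (10/5)² = 62.8, so 63 per group. This is the formula for means, as an approximation to the planned Mann-Whitney test. On it, power exceeds 99.9% even with 280 per group. Non-inferiority therefore sets the sample size.

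**3. Room for loss.**

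- One-sided 2.5%: 400 − 393 = 7 per group, or 7/400 = 1.75%.
- One-sided 5%: 400 − 310 = 90 per group, or 90/400 = 22.5%.

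**4. Power if some patients contribute no outcome.** Power = Φ(0.10 / √(0.5/n) − z₁₋α). For n = 400 at one-sided 2.5%: 0.10/0.03536 = 2.828; 2.828 − 1.960 = 0.868; Φ = 80.7%.

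| Assumed loss | n per group | One-sided 2.5% | One-sided 5% |
|---|---|---|---|
| 0% | 400 | 81% | 88% |
| 10% | 360 | 77% | 85% |
| 20% | 320 | 72% | 81% |
| 30% | 280 | 66% | 76% |

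**5. Calendar.**

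- 2-year accrual: last entry June 2022, last 5-year visit June 2027. This fits.
- 2.5-year accrual: last entry December 2022, last 5-year visit December 2027. This just fits.
- 3-year accrual: last entry June 2023, last 5-year visit June 2028, about 6 months late.

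With uniform 3-year accrual and a hard stop in December 2027, the share without a 5-year visit is 5/36 to 6/36, depending on whether the stop falls at the end or the start of that month. That is 14 to 17%, or 111 to 133 of 800. If those patients contributed nothing, 333 to 344 per group would remain, and power at one-sided 2.5% would be about 73 to 75%.

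**The case against.** **Alpha.** The article says only 5%. A reader might infer one-sided 2.5% from the two-sided 95% confidence interval under Analysis of primary endpoint, and conclude that a one-sided 5% test would contradict it. It would not: that interval is described for the proportion in each arm, not for the difference tested against the margin. One-sided 5% remains possible, and then 400 tolerates about 22% loss. This stands, and it makes the 2% figure conditional. However, the one-sided 5% reading reaches 400 only through an allowance the article does not state, while one-sided 2.5% reaches it almost directly.

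**Condensed source.** The full protocol may hold a dropout allowance, so its absence from the article is not itself a fault. The point is that the article presents 400 as the number needed and also randomises 400 per group, and its inputs reproduce that figure without any inflation.

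**Timetable.** A reader might infer that anyone randomised after December 2022 cannot have a 5-year visit. The article does not support this: the end date is an estimate, nothing makes it a stopping rule, a 5-year visit is scheduled, and accrual of up to about 2.5 years fits. Only the slow end of the stated range conflicts with the date.

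**What counts as lost.** The endpoint is cumulative and laboratory tests are done at every visit, so a deficiency recorded before exit already counts. The intention-to-treat set keeps every randomised patient, and sensitivity analyses for missing data are planned. The power figures under loss are therefore a worst case. This stands too. But patients who leave without a recorded deficiency have unknown 5-year status, and the per-protocol set drops those with missed measurements in any case.

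**Conclusion.** The point holds in conditional form. Under the reading that best reproduces 400 (one-sided 2.5%, 50% in both arms, absolute 10-point margin), the figure is essentially the evaluable number, with about 2% to spare. The plan's own provisions make it likely that fewer will be evaluable. The effect is on non-inferiority only: about 4 percentage points of power at 10% loss and 9 at 20%, as an upper bound and with assumed loss rates. The size of the intraoperative exclusions cannot be judged from the article.

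Two stronger conclusions are not supported: that the stated power is unattainable below 98% evaluable whatever the alpha, and that the end date will cut off follow-up. The first depends on an unstated sidedness, the second on accrual beyond about 2.5 years together with a hard stop. Lower power does not by itself bias the non-inferiority comparison, and weight-loss superiority is unaffected. Severity: moderate.

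**What to change.** 1. State the alpha and sidedness of the non-inferiority test, and whether 400 includes an allowance for loss.
2. Make the power statement conditional on evaluable patients. If alpha is one-sided 2.5%, for example: 393 evaluable patients per group give 80% power; with 400 per group randomised and 10%, 20% or 30% contributing no outcome (assumed rates), power is at worst about 77%, 72% or 66%. If alpha is one-sided 5%, state that 310 evaluable per group suffice and that 400 allows for about 22% loss.
3. Define the end of study as the 5-year visit of the last randomised patient, which is June 2028 or later if enrolment takes 3 years.
4. Analyse the cumulative deficiency endpoint with all available follow-up, for example as cumulative incidence, so that partly followed patients contribute.

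The cost is a less favourable power statement and possibly a later end date. No extra patients are needed.
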